## Abstract

**Rationale::**

Clinical outcomes in acute ischemic stroke due to medium vessel occlusion (MeVO) are often poor when treated with best medical management. Data from non-randomized studies suggest that endovascular treatment (EVT) may improve outcomes in MeVO stroke, but randomized data on potential benefits and risks are hitherto lacking. Thus, there is insufficient evidence to guide EVT decision-making in MeVO stroke.

**Aims::**

The primary aim of the ESCAPE-MeVO trial is to demonstrate that acute, rapid EVT in patients with acute ischemic stroke due to MeVO results in better clinical outcomes compared to best medical management. Secondary outcomes are to demonstrate the safety of EVT, its impact on self-reported health-related quality of life, and cost-effectiveness.

**Sample size estimates::**

Based on previously published data, we estimate a sample size of 500 subjects to achieve a power of 85% with a two-sided alpha of 0.05. To account for potential loss to follow-up, 530 subjects will be recruited.

**Methods and design::**

ESCAPE-MeVO is a multicenter, prospective, randomized, open-label study with blinded endpoint evaluation (PROBE design), clinicaltrials.gov: NCT05151172. Subjects with acute ischemic stroke due to MeVO meeting the trial eligibility criteria will be allocated in a 1:1 ratio to best medical care plus EVT versus best medical care only. Patients will be screened only at comprehensive stroke centers to determine if they are eligible for the trial, regardless of whether they were previously treated at a primary care center. Key eligibility criteria are (1) acute ischemic stroke due to MeVO that is clinically and technically eligible for EVT, (2) last-known well within the last 12 h, (3) National Institutes of Health Stroke Scale > 5 or 3–5 with disabling deficit, (4) high likelihood of salvageable tissue on non-invasive neuroimaging.

**Study outcomes::**

The primary outcome is the modified Rankin scale 90 days after randomization (shift analysis), whereby modified Rankin Score 5 and 6 will be collapsed into one category. Secondary outcomes include dichotomizations of the modified Rankin Score at 90 days, 24 h National Institutes of Health Stroke Score, difference between 24 h and baseline National Institutes of Health Stroke Score, mortality at 90 days, health-related quality of life (EQ-5D-5 L), Lawton scale of instrumental activities of daily living score, reperfusion quality (MeVO expanded Thrombolysis in Cerebral Infarction Score) and infarct volume at 24 h, and cost-effectiveness of endovascular recanalization. Safety outcomes include symptomatic and asymptomatic intracranial hemorrhage and procedural complications.

**Discussion::**

The ESCAPE-MeVO trial will demonstrate the effect of endovascular thrombectomy in addition to best medical management vis-à-vis best medical management in patients with acute ischemic stroke due to MeVO and provide data for evidence-based treatment decision-making in acute MeVO stroke.

**Data access statement::**

The raw data discussed in this mansucript will be made available by the corresponding author upon reasonable request.

## Rationale

In a pooled patient sample of stroke due to medium vessel occlusion (MeVO) from two prospective cohort studies, 50% of patients did not achieve excellent clinical outcome (modified Rankin Score (mRS) at 90 days with best medical management, including intravenous thrombolysis when indicated, and one-third were not functionally independent (mRS 0–2) at 90 days.^
1
^ Endovascular treatment (EVT) is a highly effective treatment for stroke due to large vessel occlusion. With both improvement in technique and development of novel devices, numerous non-randomized studies and few retrospective studies pooling data from cohort studies and randomized trials now suggest improved outcomes with EVT in stroke due to MeVO.^2–6^

However, there is a greater risk of harm related to iatrogenic vascular injury in the more distal circulation. Distal occlusions may also be more likely to recanalize with medical thrombolysis.^
7
^ Therefore, assuming there is a benefit for EVT, the magnitude of benefit is likely to be smaller than that seen in large vessel occlusion stroke. Thus, we seek to understand the balance between magnitude of effect and any safety signal when treating patients with stroke due to MeVO. The ESCAPE-MeVO trial aims to show that acute, rapid EVT in patients with acute ischemic stroke due to MeVO results in better clinical outcomes compared to best medical management.

## Methods

### Design

ESCAPE-MeVO is a prospective, randomized, open label, parallel group design study with blinded outcome evaluation (PROBE design). Patients will be screened only at comprehensive stroke centers (i.e. EVT-capable) to determine eligibility, regardless of whether they were previously treated at a primary care center (i.e. non-EVT-capable). Both patients eligible and ineligible for intravenous thrombolysis will be included in the trial. If a patient is eligible for intravenous thrombolysis, it is expected that intravenous thrombolysis will be administered without delay (see Figure 1). Ethical approval will be obtained according to local and national regulations. All patients will provide informed consent or emergency consent according to relevant national standards. After randomization, patients undergo EVT or best medical management, according to the randomization assignment. The primary outcome is 90-day neurological disability scored on the modified Rankin Scale (see Figure 2).

**Figure 1. fig1-17474930241262642:**
[figure not shown]
ESCAPE-MeVO enrollment scheme. CTP: CT perfusion; DWI: diffusion-weighted MRI (magnetic resonance imaging); h: hours; MRA: MR-angiography; NCCT: non-contrast CT; NIHSS: National Institutes of Health Stroke Scale; R: randomize. ^*^Disabling symptoms are defined by the local physicians. ^**^CT or MR angiography may be used to define MeVO location.

**Figure 2. fig2-17474930241262642:**
[figure not shown]
Patient flow in the ESCAPE-MeVO trial. D: days; DWI-MRI: diffusion-weighted MRI (magnetic resonance imaging); h: hours; MRA: MR-angiography; mRS: modified Rankin Scale; NCCT: non-contrast CT; NIHSS: National Institutes of Health Stroke Scale; R, randomization. For cases in which an MRI at 18–54 hours cannot be obtained (e.g. due to unavailability of an MR scanner, patient agitation etc.), an NCCT can be performed instead. ^*^Inclusion criteria are described in the following. ^§^In-person visit when possible. Telephone interview may be used in rare circumstances. Note that there are additional secondary outcomes not shown in the figure that are listed in the protocol.

### Patient population

Patients with acute ischemic stroke due to a clinically and technically EVT-eligible, symptomatic MeVO and reasonable likelihood of salvageable tissue on baseline neuroimaging will be included in the trial. Patients with intracranial hemorrhage, lack of salvageable brain tissue on baseline neuroimaging, severe co-morbid illnesses or severely limited life expectancy will not be eligible for the trial (see Table 1). Anatomical MeVO definitions are based on a prior publication^
8
^ and listed in Table 2.

**Table 1. table1-17474930241262642:** Inclusion and exclusion criteria in the ESCAPE-MeVO trial.

Inclusion criteria	
1	Acute ischemic stroke clinically eligible for immediate EVT, including both subjects treated and subjects not treated with thrombolytic therapy according to current standard of care. All patients eligible for intravenous thrombolysis must be thrombolyzed without delay
2	Age ⩾ 18 years at the date of randomization
3	Time from onset (or last-seen-well) to randomization < 12 h^ a ^
4	Disabling stroke defined as follows: (a) baseline National Institutes of Health Stroke Scale (NIHSS) score > 5 at the time of randomization (b) baseline NIHSS 3–5 with disabling deficit (e.g. hemianopia, aphasia, loss of hand function) as determined by the attending physician in context of the patient’s life situation at the time of randomization
5	Confirmed symptomatic and endovascularly treatable MeVO based on neurovascular non-invasive imaging (CTA or MRA)
6	Clinical deficit commensurate with MeVO location
7	Informed consent (process is site-specific)
Exclusion criteria	
1	Alberta Stroke Program Early CT Score ⩽ 5
2	Lack of salvageable brain tissue, defined as one of the following, depending on the imaging modality of the participating site: (a) NCCT + mCTA: Well demarcated hypodensity in the majority of the brain parenchyma supplied by the occluded vessel or absence of collaterals in the affected territory on the delayed phases of the mCTA (b) NCCT + (m)CTA/spCTA ± CTP: Lack of core:penumbra mismatch (if the CTP is uninterpretable, e.g. due to motion artifacts, apply exclusion criteria from 2(a). If spCTA rather than mCTA is performed, and the CTP was not performed, or was performed but is uninterpretable, score collaterals on spCTA and apply exclusion criteria from 2(a). If NCCT + mCTA + CTP are all performed, either the core:penumbra mismatch exclusion criteria from 2(b) or the exclusion criteria from 2(a) can be used) (c) MRI (DWI, MRA, ± MRP): Diffusion restriction in the majority of the brain parenchyma supplied by the occluded vessel or if MR perfusion is performed: lack of core:penumbra mismatch
3	Any evidence of intracranial hemorrhage on qualifying imaging
4	Patients living in a nursing home or requiring daily nursing care or assistance with activities of daily living
5	Patient has a major co-morbid illness, such as moderate or severe dementia, advanced cancer, advanced heart failure and so on, such that they are unlikely to be able to complete follow-up or they are unlikely to achieve the primary outcome due to the underlying illness (rather than the stroke or its treatment)
6	Pregnancy: female with positive urine or serum beta human chorionic gonadotropin (β-hCG) test
7	Participation in another clinical therapeutic intervention trial

EVT: endovascular treatment; MRA: MR-angiography; NCCT: non-contrast CT (computed tomography); CTP: CT perfusion; MRI: magnetic resonance imaging; DWI: diffusion-weighted MRI; MRP: MR perfusion; OR: odds ratio; NIHSS: National Institutes of Health Stroke Scale; mCTA: multiphase CT angiography; spCTA: single phase CT angiography.

a This choice was made based on time-windows used previously in the ESCAPE, ESCAPE-NA1 and ESCAPE-NEXT trials.

**Table 2. table2-17474930241262642:** Anatomical definitions of different MeVO locations used in the ESCAPE-MeVO trial.

MeVO location	Anatomical definition
Proximal M2 segment of the middle cerebral artery	Middle cerebral artery segments up to 1 cm distal to the main middle cerebral artery bifurcation/trifurcation
Distal M2 segment of the middle cerebral artery	Middle cerebral artery segments > 1 cm distal to the main middle cerebral artery bifurcation/trifurcation to the circular sulcus of the insula
M3 segment of the middle cerebral artery^ a ^	From the circular sulcus of the insula to the external/superior surface of the Sylvian fissure. Note that the distinction between distal M2 and M3 occlusions can be challenging. In general, the distal M2 segment has a more vertical course in the coronal plane, while the M3 segment has a more horizontal course, as it extends from the circular sulcus laterally to the cortical surface. This can be helpful in ambiguous cases
A2 segment of the anterior cerebral artery	From the origin of the anterior communicating artery to the origin of the callosomarginal artery
A3 segment of the anterior cerebral artery	From the origin of the callosomarginal artery to the artery’s posterior turn above the corpus callosum
P2 segment of the posterior cerebral artery	From the origin of the posterior communicating artery to point of entrance in the quadrigeminal cistern
P3 segment of the posterior cerebral artery	Segment within the quadrigeminal cistern

a Note that a non-dominant third-order middle cerebral artery third-order branch proximal to the circular sulcus of the insula will also be considered an M3 occlusion.

### Randomization

Treatment will be assigned using 1:1 randomization (best medical care control: EVT intervention) centrally, using a web-based algorithm. Randomization assignment will be fully concealed by having dynamic real-time allocation, based upon random number generation. The treatment will be unblinded (open-label). To minimize differences between the two treatment arms of the trial other than the investigational treatment, a randomized minimization procedure will occur on five baseline prognostic variables, namely age, sex, baseline NIHSS, occlusion location (anterior vs middle vs posterior cerebral artery), and site (minimal sufficient balance).^
9
^

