### Statistical analysis

The primary population for analysis will be the intention to treat population (as randomized) defined according to randomization assignment. The primary outcome (ordinal mRS at 90 days with mRS 5 and 6 collapsed into a single category) will be analyzed using a multivariable proportional odds model, adjusting for the five variables used in the minimization algorithm. A Wald test will be used to assess the hypothesis that the common odds ratio for an improvement in one or more points on the mRS scale is greater than 1. The primary analysis will be supported by an assessment of the unadjusted odds of achieving the primary outcome using an unadjusted comparison of proportions with the Wilcoxon rank sum test. The formal null and alternative hypotheses are as follows:

H_0_: The common odds ratio comparing treatment to control for improvement in one or more points on the mRS scale at 90 days, where categories 5 and 6 are collapsed, is not different from 1.H_A_: The common odds ratio comparing treatment to control for improvement in one or more points on the mRS scale scored at 90 days, where categories 5 and 6 are collapsed, is greater than 1.

Pre-specified subgroup analyses will be performed stratified by intravenous thrombolysis and other key variables. Further details of the analysis plan are documented in a Statistical Analysis Plan that will be finalized prior to database lock.

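### The primary model adjusts for occlusion location by arterial territory only and not for thrombolysis: a small, cheaply avoided loss of efficiency, not a validity error

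*Protocol article*

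**What the plan says.** The Randomization section lists the minimization factors: age, sex, baseline NIHSS, "occlusion location (anterior vs middle vs posterior cerebral artery), and site (minimal sufficient balance". The Statistical analysis section specifies the primary analysis as a proportional odds model of the 90-day mRS, with scores 5 and 6 combined, "adjusting for the five variables used in the minimization algorithm". These are stated choices about the primary analysis, not details left open.

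Table 2 (Patient population) defines seven segments: proximal M2, distal M2, M3, A2, A3, P2 and P3. Three of them lie within the middle cerebral artery. A footnote-type remark on M3 adds: "Note that the distinction between distal M2 and M3 occlusions can be challenging".

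On thrombolysis, the Design section says: "Both patients eligible and ineligible for intravenous thrombolysis will be included in the trial". The Rationale says: "Distal occlusions may also be more likely to recanalize with medical thrombolysis". Thrombolysis appears in the analysis only here: "Pre-specified subgroup analyses will be performed stratified by intravenous thrombolysis and other key variables". The other subgroup variables are not named, and further detail is left to a SAP that is not shown.

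**The concern.** In an ordinal model, leaving out a baseline variable that predicts the outcome costs power and pulls the odds ratio towards 1. The article itself links distality and thrombolysis to recanalization, which makes both plausible predictors of the 90-day mRS. It also considers thrombolysis important enough to be its one named subgroup variable.

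The five-factor model nevertheless gives an occlusion within 1 cm of the bifurcation and an M3 occlusion the same location value, and it makes no use of thrombolysis status. The design has little power to spare, so the question is how much this omission costs and whether it is easily recovered.

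**Working it through.** **1. The plan's own figure.** Inputs from Sample size estimates: mRS 0/1/2/3/4/5-6 of 34/28/11/8/7/12% (EVT) and 24/26/8/12/18/12% (control), 85% power, two-sided alpha 0.0398.

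- A maximum-likelihood proportional odds fit to these distributions gives a common OR of 1.633, log OR 0.490.
- The mean category proportions are 0.29, 0.27, 0.095, 0.10, 0.125 and 0.12. Their cubes sum to 0.0496, so 1 − 0.0496 = 0.950.
- Whitehead's formula: N = 12(z_α + z_β)² / [(log OR)² × 0.950] = 12(2.056 + 1.036)² / (0.490² × 0.950), which is 502 with unrounded inputs, against 500 stated.
- Power at N = 500 is 84.9% by formula and 84.3% by Wilcoxon simulation.
- The standard error of the log OR at N = 500 is √[12/(500 × 0.950)] = 0.159.

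The stated size is reproduced. It does not depend on the covariates.

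**2. Size of a chance imbalance.** For a factor with prevalence p that is left to chance, the between-arm difference has SE = √[4p(1 − p)/500], and its 95% limit is 1.96 × SE. The article gives no prevalences, so p is assumed.

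- p = 0.3: 8.0 points
- p = 0.5: 8.8 points
- p = 0.6: 8.6 points

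The probability of a gap above 10 points is 1.5% to 2.5%. To first order, an 8.8-point gap moves the treatment log OR by 0.088 × 0.4 = 0.035 or 0.088 × 0.8 = 0.070. The larger value is 0.070/0.159 = 0.44 of a standard error.

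**3. Cost of omission.** Simulated trials of 500 patients (250 per arm) used the control distribution above, a true treatment log OR of ln 1.63 = 0.489, and two-sided alpha 0.0398, with 1,500 runs per scenario. Assumptions: 40% distal, 50% thrombolysed, independent of each other, each with the stated log OR on the mRS. A model with treatment alone was compared with one that also contains both factors.

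| Log OR of each factor | Power, omitted | Power, included | Mean treatment log OR, omitted | Included |
|---|---|---|---|---|
| 0 | 83.5% | 83.7% | 0.489 | 0.490 |
| 0.4 | 83.5% | 84.2% | 0.482 | 0.492 |
| 0.8 | 79.6% | 83.9% | 0.459 | 0.491 |

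The attenuation is (0.489 − 0.482)/0.489 = 1.4% at log OR 0.4 and (0.489 − 0.459)/0.489 = 6.1% at 0.8. With no treatment effect, rejection was 3.3% to 4.5% across both models, against a nominal 3.98%. The simulation error of that rate is √(0.0398 × 0.9602/1500) = 0.5 points, so the type I error is intact either way.

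Two limits apply. Each power figure has a simulation error of √(0.84 × 0.16/1500) = 0.9 points. Both models were fitted to the same simulated data, so their difference is more precise than that, but 0.7 should still be read as small rather than exact. The other minimization factors were not simulated.

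**4. Cost of inclusion.** Location with four levels uses three parameters instead of two, and thrombolysis uses one: two extra parameters in about 500 patients.

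**The case against.** The strongest case for the plan is that adjusting for exactly the minimization factors is standard, that the gain is modest and rests on assumed effects, and that distal M2 and M3 are hard to tell apart. The last point is a sound reason for coarse coding in real-time allocation. It is also a reason to merge those two segments in the model, but not to ignore the proximal M2 boundary, a 1 cm rule that carries no such caveat.

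Several stronger readings are tempting and are not supported:

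- **A gradient of harm within MeVO.** The Rationale does say "there is a greater risk of harm related to iatrogenic vascular injury in the more distal circulation", but it goes on to conclude that benefit is likely smaller than in large vessel occlusion. The contrast is with large vessels, and a proximal-M2-to-M3 gradient is an inference. The Rationale does not mention spontaneous recanalization or name thrombolysis as a cause of harm. Its stated goal concerns all MeVO patients.
- **Biased by imbalance.** A chance gap of 8 to 9 points is ordinary sampling variation, already reflected in the standard error.
- **A defective minimization scheme.** The choice of factors is a trade-off, and the article shows no error in it.
- **Neglected effect modification.** Main-effect adjustment would not address it. Subgroup analyses would, and segment may be among the unnamed key variables.
- **A subgroup defined after allocation.** Inclusion criterion 1 treats thrombolysis as an entry characteristic. The article does not say that it always precedes randomization, but neither does it define the subgroup by later treatment. That definition belongs to the SAP.

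One further caution stands: the article defines segments but does not say that each patient's segment is recorded, or recorded before allocation.

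**Conclusion.** The point holds as a low-cost improvement to the primary model. As specified, the model makes no use of thrombolysis status or of position within the middle cerebral artery, two baseline features that the article itself treats as relevant. No contradiction or invalid test follows, and a reader should not infer that the primary result would be biased.

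The loss is about 0.7 to 4 points of power and about 1% to 6% attenuation of the log odds ratio. These figures assume a log OR of 0.4 to 0.8 for each factor, 40% distal, 50% thrombolysed, and independence of the two. If neither factor predicts the outcome, there is nothing to gain and practically nothing to lose. With planned power of 84.9% at 500 patients, the upper end is worth recovering.

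**What to change.** Leave the allocation algorithm unchanged. Before database lock, in the SAP that the article says will be finalized by then, amend the primary model as follows:

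- Add intravenous thrombolysis given or decided before randomization (yes/no).
- Replace the three-level location covariate with four levels: proximal M2 / distal M2 or M3 / ACA / PCA. These are nested in the minimization factor, so the model still adjusts for it. Segment should be read from baseline imaging without knowledge of the assigned arm, because the trial is open-label.
- Keep age, sex, baseline NIHSS and site as they are.

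The change should be settled by people who have not seen outcomes by arm, since an interim analysis is planned.

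The cost is two extra parameters and some remaining misclassification of segment. The adjusted odds ratio becomes conditional on slightly more covariates, so it is not exactly the same quantity as under the five-factor model. The change also depends on both variables being recorded as of randomization. If that cannot be established for one of them, that variable should stay out of the primary model.

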### Intervention

Patients will be randomized to receive routine medical stroke care (control group) or to EVT plus medical care (intervention group). EVT will be performed using any Solitaire stent-retriever device (Solitaire X, Medtronic) as the first-line approach. Any combination of additional devices (e.g. aspiration and balloon guide catheters) may be used. In case the first-line attempt is unsuccessful, other stent-retrievers or aspiration catheters may also be used at the discretion of the neurointerventionalist. The use of general anesthesia versus conscious sedation or local anesthesia is considered a local decision according to the judgment of the local team. We expect that access to more distal parts of the intracranial circulation may require greater use of general anesthesia to allow for a completely still patient as compared to EVT for large vessel occlusion stroke.

Medical care is expected to apply to all patients and should include stroke unit care, early rehabilitation, investigations for stroke mechanism, stroke prevention treatment, and vascular risk reduction.

